**Methods**

Primary aim:

To collect high quality and relevant data regarding global surgery exposure for medical students across the world in order to establish an international framework

Secondary Aims:

To examine students’ awareness of the key messages of the Lancet Global Surgery Commission

To characterise the proportion of medical students who would want to be involved in global surgery in their future career

To ascertain perceived barriers to becoming involved in global surgery

Study Design

The International Survey Of Medical students Exposure to Relevant global Surgery (ISOMERS) study is an online, international, multi-centre, questionnaire-based study evaluating global surgery exposure and career aspirations among final year medical students across the world. Data will be collected on the demographics of participants, their exposure to global surgery, their awareness of the key messages of the Lancet Global Surgery Commission, and their career aspirations. The questionnaire will be disseminated by email and social media through collaborative university medical school and student networks, such as the network of InciSioN National Working Groups (NWGs) across the world. The generic collaborative method, and the benefits that participating students derive from it are based on previous well-documented literature.

Study Population

All medical schools across the world will be eligible to participate. Participant eligibility will be determined according to pre-specified criteria. Responses will be excluded if the participant did not meet the inclusion criteria or met the exclusion criteria. Participation rates will be calculated as the total number of eligible participants over the total number of final year medical students at participating medical schools. The minimum sample size required from our target population for a margin of error of 5% and a confidence level of 95% is 377 assuming a 50% response distribution for each question.

Inclusion criteria:

All final year medical students across the world

Exclusion criteria:

Listed as a collaborative author or named author on any publications from this study.

Primary Outcomes

The proportion of students that have had exposure to global surgery in each country.

The range of modalities utilised by medical students to gain exposure to global surgery.

The percentage of students that prefer each modality.

Secondary Outcomes

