**Conclusion**

The International Survey Of Medical students Exposure to Relevant global Surgery (ISOMERS) will establish whether medical students are exposed to global surgery during medical school, how they are exposed to global surgery, whether the types of exposures meet the needs of students, current global surgery knowledge among students, and career aspirations among students and doctors. This is the first such an endeavour has been undertaken internationally. Our results will allow us to draw comparisons between countries.

*Appendix S2*

PDF attachment

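### The 377 minimum gives its 5% margin for one pooled worldwide proportion, not for the per-country primary outcome or the country comparisons that the protocol promises without condition

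*Protocol*

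**What the plan says.** Protocol, Methods, Study Population gives the only sample size in the document, which "for a margin of error of 5% and a confidence level of 95% is 377". That sentence ties the figure to the population as a whole, opening with "The minimum sample size required from our target population". The proportion behind the calculation is a conventional worst case, given as "assuming a 50% response distribution for each question". The inclusion criterion in the same section defines whom the figure covers: "All final year medical students across the world".

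Methods, Primary Outcomes lists three outcomes. The first is "The proportion of students that have had exposure to global surgery in each country". The other two, the range of modalities and the percentage preferring each, are not defined by country.

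Methods, Data collection makes the country the working unit, since each national working group runs the survey in its own country. The Conclusion states: "Our results will allow us to draw comparisons between countries".

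The protocol gives no number of participating countries, no minimum or margin per country, and no precision for a difference between countries.

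**The concern.** The only stated precision belongs to a single worldwide proportion, while the first-listed primary outcome is a set of proportions, one per country. A survey that reached its own minimum could report every country far less precisely than the 5% in the protocol, and a reader of the results would have no warning of it. The Conclusion then treats those country figures as fit for comparison, whatever their size.

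The consequence is practical. The Summary says that the results will guide where the network gives educational support. A country figure resting on a few respondents could steer that support wrongly.

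**Working it through.** **Inputs from the protocol (Methods, Study Population).** Margin d = 0.05; 95% confidence, so z = 1.96; p = 0.50; stated minimum 377.

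**Assumptions, because the protocol gives no figures.** The number of countries k, an equal split of 377 among them, and the number N of final-year students in a population. The formulas also take respondents as a simple random sample.

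**1. Reproduce 377.** n0 = z²p(1−p)/d² = 1.96² × 0.25 / 0.05² = 384.1, rounded up to 385. With the finite population correction, n = n0/(1 + (n0 − 1)/N); at N = 20,000 this is 376.9, so 377. Without the correction, 377 respondents give 1.96 × √(0.25/377) = 5.05 points. The figure is therefore right for one pooled proportion.

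**2. Precision by country at the stated minimum.** With n = 377/k, the half-width for one country is 1.96 × √(0.25/n), and for a difference between two countries 1.96 × √(0.5/n).

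| Countries (k) | n per country | Half-width, one country | Half-width, difference |
|---|---|---|---|
| 2 | 188.5 | 7.1 points | 10.1 points |
| 5 | 75.4 | 11.3 points | 16.0 points |
| 10 | 37.7 | 16.0 points | 22.6 points |
| 20 | 18.85 | 22.6 points | 31.9 points |

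An unequal split leaves the smaller countries worse off than the table shows.

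**3. Can the finite population correction restore 5 points?** Multiply the half-width by √((N − n)/(N − 1)), set the result to 0.05 and solve for N.
- k = 10: (N − 37.7)/(N − 1) = (0.05/0.1596)² = 0.098, so N is about 42. About 38 of 42 students would have to answer.
- k = 2: (N − 188.5)/(N − 1) = (0.05/0.0714)² = 0.491, so N is about 369. About half of all final-year students in each country would have to answer.

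**4. What a 5% margin in each country would need.** Before correction, 385 per country: 385 × 10 = 3,850 for 10 countries and 385 × 20 = 7,700 for 20. With the correction, 278 if a country has 1,000 final-year students, 357 if 5,000 and 370 if 10,000.

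**5. A looser threshold.** A 10-point margin needs 1.96² × 0.25 / 0.10² = 96.04, so 97 respondents before correction. Two such countries would be compared with a half-width of 1.96 × √(0.5/97) = 14.1 points.

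**The case against.** The best defence is that the protocol never claims a 5% margin for each country. Its minimum is tied to the target population, which reads naturally as pooled. It is also a floor: all medical schools are eligible, dissemination is at least weekly for six weeks, and the Project Timeline allows data collection to be extended. The analysis is mainly descriptive, and interval methods or small-country rules could sit in a statistical analysis plan that is not at hand.

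Much of this stands, and it rules out several stronger readings that a reader might infer.

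- *That 377 is claimed as sufficient for each question.* In the sample size sentence that phrase qualifies the assumed 50% response, not the minimum.
- *That the margin fails for all the primary outcomes.* Only the first is defined by country. The percentage preferring each modality can carry the pooled margin under simple random sampling.
- *That the country figures would be mostly noise.* This depends on the true spread between countries, which is unknown. At k = 10 the sampling standard error is √(0.25/37.7) = 8.1 points. If the true standard deviation between countries were 20 points (assumed), 400/(400 + 66) = 86% of the observed variance would be real; if 5 points, 25/(25 + 66) = 27%.
- *That testing every pair of countries would produce many false positives, or that countries would be ranked.* The protocol plans neither.
- *That 385 respondents are needed in every country.* The finite population correction lowers this, as shown above.

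The defence does not remove the mismatch. The protocol itself fixes the sample size, the per-country outcome and the unconditional comparison statement. No later analysis plan can make 377 respondents deliver 5 points in each of several countries of ordinary size. Recruitment above the floor would help, but nothing directs it to any particular country.

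**Conclusion.** The concern holds as a mismatch of scope; 377 is not an arithmetical error. At the stated minimum, the 5% margin does not hold for the first primary outcome once respondents are spread over two or more countries, apart from near-census sampling in very small ones. Under an equal split, a country's margin is roughly 1.4 times the stated one with 2 countries (7.1/5) and 4.5 times with 20 (22.6/5). The unconditional comparison statement in the Conclusion is therefore not supported at that size.

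The size of the shortfall rests on the assumed number of countries, the equal split and recruitment stopping at 377; it shrinks if recruitment runs well above the floor in the countries concerned. This should be fixed, but for a descriptive survey, where rewording and modest reporting rules suffice, it is not a defect that invalidates the study.

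**What to change.** 1. In Methods, Study Population, state that the 5% margin at 377 applies to pooled proportions only and not to the per-country primary outcome.
2. Report every country's proportion with its n and a 95% Wilson interval, which behaves acceptably in small samples.
3. In the Conclusion, make the comparison statement conditional on country sample size. Limit named between-country comparisons to countries that reach a precision fixed before country results are seen, and group the rest by region or income group. A 10-point margin, about 97 respondents before finite population correction, is one workable threshold; the choice is the sponsor's.
4. Optionally, estimate country proportions from a logistic model with a random intercept for country, so that small countries are shrunk towards the overall mean.

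The cost is rewording and a modest amount of extra analysis, with no extra recruitment. The downside is that some small countries will not be compared individually.

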The proportion of students aware of the key messages of the Lancet Global Surgery Commission

The proportion of students who do not want to pursue a career in global surgery.

The range of barriers identified by medical students to pursuing a career in global surgery.

Methods for recruiting participants

All final year medical students at any medical school in the world will be eligible to participate. Medical students will be invited to participate in the study by email and social media.

In addition, final year medical students enrolled in any medical school in the world may be invited to collaborate in the study as regional leads as described in Table 1. Collaborators will ensure that the steering committee possess accurate data about the number of final year medical students at their institution, and they will be primarily responsible for disseminating this questionnaire amongst students at their medical school.

Financial and other rewards to participants

No financial or other rewards will be offered to participants.

Data collection

ISOMERS will be delivered by NWGs of InciSioN. Each NWG will be responsible for conducting ISOMERS within their country and disseminating the questionnaire. Medical students enrolled in any medical school may be invited to collaborate in this study as regional leads who are coordinated by the appropriate NWG. The role of a regional lead would be to identify the number of final year medical students at their institution and to disseminate the questionnaire among students at their medical school. Dissemination will be done using any online tools such as social media and mailing lists. The questionnaire must be disseminated by regional leads using all online tools available to them at least once a week for 6 consecutive weeks. Regional leads must share evidence to show that they have done to this to their appropriate NWG to be awarded collaborator status within our collaborative authorship model.

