The online questionnaire utilises a combination of the Likert scale, multiple choice options and free text questions in order to broaden the capture and improve granularity of the data. The questionnaire is divided into four major sections: background information, provision of global surgery teaching, knowledge about global surgery and career aspirations. All sections of the questionnaire must be completed for the answers to be deemed eligible. Following data collection, the data will be validated and analysed by the steering committee. The questionnaire has been sent to multiple medical students who were not involved in creating the data collection proforma. Their responses were evaluated for potential problems, and the questionnaire was updated to ensure the questions were relevant, comprehensive and accessible.

Medical schools will be able to request for their own specific data and the analysis done on said data from the ISOMERS steering committee following study completion. InciSioN NWGs will be able to request for their country specific de-identified and pseudo-anonymised data.

Information Governance

No identifiable information will be collected. No individual medical school data will be published with the exception of case studies with permission from the medical school. Data will be collected using a structured standard questionnaire. All data will be pseudo-anonymised. Providing personally identifying data (i.e. contact details) will be optional and will not be linked to the questionnaire answers given. All other data collected may be used for research purposes. Data will be stored securely and accessible only by the primary researchers and users nominated by them. At the end of the project, the data will be stored for five years after final publication.

Statistical Analysis

The resultant data will be analysed via descriptive statistics. For quantitative data where possible, ANOVA tests will be used for parametric data and the Wilcoxon signed-rank test will be used for non-parametric data. For Likert scale data, a multinomial regression will be utilised.

Authorship

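### Weekly re-posting on every channel, with unlinked answers and no one-response rule, allows repeat responses that could not be reliably identified afterwards

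*Protocol*

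**What the plan says.** Protocol, Methods, Data collection sets the posting rule: "The questionnaire must be disseminated by regional leads using all online tools available to them at least once a week for 6 consecutive weeks". On channels it says: "Dissemination will be done using any online tools such as social media and mailing lists". Leads must show evidence of posting "to be awarded collaborator status within our collaborative authorship model".

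Under Information Governance the protocol says "No identifiable information will be collected", and that giving contact details is "optional and will not be linked to the questionnaire answers given". The same section says that the data are pseudo-anonymised, but it describes no record code or key.

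Under Study Population: "Responses will be excluded if the participant did not meet the inclusion criteria or met the exclusion criteria". Inclusion is being a final-year medical student. The one exclusion is being an author or collaborative author on the study's publications. Neither criterion mentions a repeat response. Data collection adds that all sections must be completed and that the steering committee validates the data. It does not say what validation covers.

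**The concern.** Weekly reminders are ordinary survey practice and are not the fault. The gap is that they are combined with unlinked answers and no rule that a student counts once. A student could answer from a mailing list in week 1 and from social media in week 5, and the protocol names nothing that would show the two records to be the same person.

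The exclusion promise has a related weakness. Final-year status can rest only on what the respondent declares. Authorship status cannot be matched to unlinked answers, and leads earn it only after six weeks of posting, so a lead who answers early may not know whether the exclusion applies.

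The quantities at stake are the first primary outcome (the exposure proportion by country), the participation rate, the count towards 377, and the comparisons between countries that the Conclusion intends. This cannot be left to a later analysis plan, because analysis cannot create a key that was never collected.

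**Working it through.** **Inputs from the protocol (Study Population, Primary Outcomes):** minimum 377, margin of error 5%, confidence 95%, response distribution 50%; participation rate = eligible participants / final-year students at participating schools; exposure proportion reported by country.

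**Assumed, because the protocol gives no figure:** share of records that are repeats f = 2%, 5%, 10%; true exposure p = 30%; exposure among repeats q = 60%, with q = 100% as the extreme.

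**The plan's own figure.** n0 = 1.96² × 0.25 / 0.05² = 384.1, that is 385 without a finite-population correction. With the correction n0 / (1 + (n0 − 1)/N), an assumed population N of 20,000 gives 376.9, that is 377. The figure reproduces. It presumes 377 different people.

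**Effects that do not depend on the answers.**
- Different students among 377 records: 377 × (1 − f).
- Inflation of the participation-rate numerator: 1 / (1 − f).
- Effective sample size if the repeats stay in, each repeater appears twice and gives the same answer both times: 377² / [377(1 − 2f) + 4 × 377f] = 377 / (1 + 2f).
- Margin at 50%: 1.96 × √(0.25 / effective n). With no repeats, ignoring the finite-population correction, this is 5.05 points.

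**Effect that depends on the answers.** Bias in the exposure proportion = f × (q − p).

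| f | Repeats in 377 | Different students | Numerator inflated by | True margin (points) | Bias, q = 60% (points) | Observed proportion, q = 100% |
|---|---|---|---|---|---|---|
| 2% | 8 | 369 | 2.0% | 5.15 | 0.6 | 31.5% |
| 5% | 19 | 358 | 5.3% | 5.29 | 1.5 | 33.5% |
| 10% | 38 | 339 | 11.1% | 5.53 | 3.0 | 37.1% |

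The last column is (0.30 × different students + repeats) / 377; at 5% this is (0.30 × 358 + 19) / 377 = 33.5%. If q = p, the bias is 0 at every f.

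**Small country samples.** With an assumed 9 of 30 exposed (30.0%), three extra exposed records give 12/33 = 36.4%. A few records matter far more here than in the pooled sample.

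**The case against.** The strongest case against is that the protocol is silent rather than wrong. The questionnaire, the platform settings and any SAP are not shown, and a screening item or one-response setting may exist there. Participants have little reason to answer twice: "No financial or other rewards will be offered to participants", and every section must be completed. The authorship incentive rewards posting, not answering.

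Much of this stands, and it limits what can be claimed. A reader might infer any of the following, and the protocol supports none of them:

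- **An unrestricted public link is used.** The protocol does not say so. It is a reasonable inference from the channels, but leads are asked to reach students at their own school.
- **Repeats and ineligible records cannot be removed.** This is too strong. There is an exclusion rule, a validation step, a background section that could support rough matching, and pseudo-anonymised data that may imply a code. What is missing is any stated method or any reliable key.
- **The exposure proportions are distorted upwards.** This is a risk of unknown size. The bias is zero if repeaters resemble the rest, and the 31.5% to 37.1% range takes every repeater as exposed. Ineligible earlier-year students could be less exposed, which would pull the other way.

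What the objection does not remove is that the protocol prescribes repeated multi-channel contact and unlinked answers, yet sets no rule that a student counts once.

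**Conclusion.** The concern holds as a gap in control, and it should be closed before launch. Followed as written, the plan allows repeat responses that could not be reliably identified later. Any repeats overstate the participation rate, progress towards 377 and precision: at an assumed 5%, about 358 students stand behind 377 records and the true margin is about 5.29 rather than 5.05 points. Bias in the exposure proportion is conditional: 0 if repeaters are like other respondents, and about 1.5 points at 5% repeats with 60% against 30% exposed. In the pooled sample that is well inside the planned 5-point margin; in a country with some 30 respondents a handful of records could move the estimate by more. All repeat rates and exposure differences are assumptions. The protocol offers no evidence that repeats will be common, and the effect of ineligible responses cannot be sized from it.

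**What to change.** Before launch:

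1. Open the questionnaire with mandatory self-declared items on final-year status and on any regional-lead or collaborator role, ending the survey for ineligible respondents. Align the authorship exclusion with the role item, since some leads will not earn author status.
2. Switch on the platform's one-response setting. This is a partial control only; it does not stop a student who uses a laptop and then a phone.
3. Add a self-generated non-identifying code built by a fixed rule. Count only the first complete response per school and code, and remove the code before the anonymised dataset is released.
4. Add to the exclusion criteria: *a second or later response from the same student*. Report a sensitivity analysis without suspected duplicates, for example records that agree on all background items under different codes.

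The cost is a platform setting, a few short items, one exclusion line and one extra analysis. A few genuine responses may be lost to shared devices or to code collisions within a school. Final-year status remains self-reported.

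### The named tests have no term for school although students are reached largely through their schools, and the signed-rank test does not suit independent respondents measured once

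*Protocol*

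**What the plan says.** Methods, Statistical Analysis, makes description the default: "The resultant data will be analysed via descriptive statistics". It then names three methods: "For quantitative data where possible, ANOVA tests will be used for parametric data", with the Wilcoxon signed-rank test as the non-parametric counterpart, and "For Likert scale data, a multinomial regression will be utilised". It gives no school term, random effect, robust variance or design effect, and it names no grouping factor for any test.

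The first primary outcome is a proportion per country: "The proportion of students that have had exposure to global surgery in each country". A secondary outcome is also a proportion: "The proportion of students who do not want to pursue a career in global surgery". The Conclusion expects the results to support comparisons between countries.

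Under Methods for recruiting participants and Data collection, regional leads circulate the questionnaire within their own schools, coordinated by national working groups. Students are also invited by email and social media. Leads report class sizes: "Collaborators will ensure that the steering committee possess accurate data about the number of final year medical students at their institution". Study Population uses these as the denominator of the participation rate. School must be recorded for each respondent, because Data collection promises: "Medical schools will be able to request for their own specific data and the analysis done on said data".

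**The concern.** Classmates share a curriculum, and one of the four questionnaire sections asks about the teaching provided. Their answers on exposure can therefore be expected to resemble each other more than those of students at different schools. Schools are nested in countries, so variation between schools feeds directly into the apparent variation between countries. A method that counts every student as an independent observation understates that variation. At stake are the width of each country's interval and the error rate of any country comparison. One well-taught school with many responders could pass for a country effect.

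The signed-rank test is a separate matter. It compares two measurements on the same person, or one sample against a fixed value. This survey measures each respondent once and compares independent people, so the test does not match the data.

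**Working it through.** **The plan's own figure.** Study Population gives 377 for a 5% margin, 95% confidence and a 50% proportion. The formula n = z²p(1−p)/e² gives 1.96² × 0.25 / 0.05² = 384.15. With a finite-population correction and an assumed population of 20,000, 384.15 / (1 + 383.15/20,000) = 376.9, which rounds up to 377. The figure reproduces as a simple random sample, so the plan's only precision calculation also treats students as independent. Without the correction, 377 responses give ±5.05 points.

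**Inputs not in the documents.** The ICC, the number of countries, the schools per country and the responders per school are all assumed. The main layout is 10 countries × 3 schools × 12 students = 360 responses, close to 377, with 30% exposed everywhere and no true country difference.

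**Formulas.** Design effect DE = 1 + (12 − 1) × ICC. Effective sample = 377/DE. Half-width = 5.05 × √DE. As a rough check on the false-positive rate with 10 countries, the 5% critical value of chi-square on 9 degrees of freedom is 16.92, so the rate is approximately P(χ²₉ > 16.92/DE). The last column is a beta-binomial simulation of a student-level F-test at 5%, with 4,000 runs per setting.

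| ICC | DE | Effective sample | Half-width (points) | Rough false-positive rate | Simulated |
|---|---|---|---|---|---|
| 0 | 1.00 | 377 | 5.05 | 5% | about 5% |
| 0.01 | 1.11 | 340 | 5.3 | 8% | about 9% |
| 0.05 | 1.55 | 243 | 6.3 | 28% | about 29% |
| 0.10 | 2.10 | 180 | 7.3 | 53% | about 54% |
| 0.20 | 3.20 | 118 | 9.0 | 81% | about 83% |

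**Fewer countries.** With 2 countries, 4 schools each, 10 students per school and a 50% proportion, the simulated rates at ICC 0, 0.01, 0.05, 0.10 and 0.20 are 5.5%, 6.8%, 10.8%, 17.2% and 27.0%. The formula 2(1 − Φ(1.96/√DE)), with DE = 1.09, 1.45, 1.90 and 2.80, gives 6.0%, 10.4%, 15.5% and 24.1% for the four positive ICCs.

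**Is the yes/no scale to blame?** No. At ICC 0 the F-test on 0/1 data keeps about 5%. With 10 countries × 4 schools × 10 students and ICC 0.10, the F-test gives 46.6% and a student-level chi-square test 46.3%. The inflation comes from the ignored clustering.

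**Do the usual remedies work here?** An F-test on school-level proportions holds about 5 to 6% in every setting tried. A cluster-robust Wald test of country does not: it gives 64 to 69% false positives with 10 × 3 × 12 and over 99% with 20 × 2 × 9. Intervals built separately for each country from the normal distribution cover about 77% with three schools and 56% with two; dividing the variance by the number of schools minus one lifts the latter to about 66%. In the same simulation, intervals from the between-school variance pooled over countries, with a t reference, cover about 95%. The random-intercept logistic model was not simulated.

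**The case against.** The strongest reply is that the protocol never states the analysis simulated here. It confines ANOVA and the signed-rank test to quantitative data where possible, makes description the default, and names no formal country test. A proportion per country can simply be reported. This stands, and it rules out three stronger readings that a reader might infer:

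- That ANOVA is assigned to yes/no exposure. It is not; those outcomes have description but no suitable named test.
- That country differences will be declared falsely. Only *may* is supportable, because the result depends on an ICC and a layout that the documents do not give.
- That schools determine exposure. The protocol does not say so. The primary outcomes also cover ways in which students themselves seek exposure, so correlation within school is a reasonable expectation and not a stated fact.

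It is also fair that open email and social-media invitations may bring in students from schools without a lead, so recruitment is not wholly school by school. Class size is not unused either, since it enters the participation rate.

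Finally, a statistical analysis plan that is not shown may handle clustering. That would answer a complaint about missing detail. It does not remove the need to correct methods that the protocol already names, and the signed-rank test is wrong for this design whatever such a plan adds. Description alone does not escape the problem: a country's interval computed as if students were independent is too narrow even if no test is run.

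**Conclusion.** The point holds in a limited form. The protocol names methods without a school term for a study that reaches students largely through schools and intends to compare countries. It names no test suited to the yes/no outcomes, and it names a paired-data test for unpaired data. Under any positive within-school correlation, intervals are too narrow and student-level country comparisons are anti-conservative.

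The size is uncertain. It runs from slight (two countries, ICC 0.01) to severe (ten countries, ICC 0.10 or more), and every figure rests on assumed ICCs and layouts. The error in the signed-rank test rests on no such assumption.

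**What to change.** Revise the Statistical Analysis section as follows.

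- **Yes/no outcomes compared between countries:** a logistic model with country as a factor and a school random intercept, or an analysis of school-level proportions. Base country intervals on the between-school variance pooled across countries, which assumes that this variance is similar from country to country.
- **Likert items:** add a school random effect to the multinomial model.
- **Non-parametric comparisons:** replace the signed-rank test with the rank-sum test (two groups) or the Kruskal-Wallis test (more than two), applied to school-level summaries when countries are compared. At student level these tests would ignore clustering too.
- **Few schools:** do not rely on uncorrected cluster-robust or GEE standard errors where countries have only a few schools. Report one-school countries descriptively, without a test.
- **Class-size weighting:** at most a sensitivity analysis, limited to schools whose lead supplied the class size. It does not correct for self-selection within a school.

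The main changes are to wording and need no new data, since school must already be recorded. The price is wider intervals and fewer countries that can be formally compared.
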